## Methods

### Study design

The study was designed as a pragmatic, multi-site, randomized controlled trial of the 'Don't Panic' course versus a wait-list control group. Measurements were taken at baseline measurement (T0) followed by a posttest measurement after three months (T1). To monitor effect maintenance over time, the experimental group underwent a prolonged follow-up measurement nine months after baseline, i.e., six months after the end of the intervention (T2). The study was designed to mimic the Dutch health care system as naturalistically as possible in terms of patient recruitment and the manner in which intake, offering the intervention, and monitoring outcomes are conducted. This was done to enhance external validity. The randomization took place after administration of the International Neuropsychiatric Interview Plus (MINI-Plus; [24]), and was carried out centrally by an independent third party. A blocked randomization scheme was used, stratified by mental health centre, subthreshold PD versus mild PD, and by presence versus absence of co-occurring agoraphobia. The latter was included because it was assumed that agoraphobia may be a prognostically relevant factor for outcome in PD. This procedure ensures that participants with and without PD or agoraphobia were equally distributed across both trial arms. See Figure 1 for participants' flow through the study. The trial protocol was approved by an independent medical ethics committee (METIGG).

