### Sample size

Power analysis indicated that 129 participants per condition are required in order to detect a difference in symptom reduction, equivalent to a standardized effect size of at least 0.35 in a two-sided test at alpha = 0.05 and a power of (1-beta) = 0.80.

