The following costs are examined for economic evaluation: costs directly related to health care, indirect health care related costs (out-of-pocket costs, costs of informal care), direct costs outside health care (monetary value of production losses caused by absence and reduced productivity), as measured with the TIC-P. The mean total costs for each of the conditions at baseline and T1 were calculated. Then the pre-post difference in costs were calculated to obtain the increase (or decrease) of costs over time in each of the conditions. First, we observed how many participants presented with a clinically significant change on the PDSS-SR across the two groups. The incremental cost-effectiveness ratio (ICER) was calculated as the incremental costs for a health gain of a clinically significant change over three months. Next, we observed how many people stayed PD free at T1. The ICER was calculated as the incremental costs for a health gain of a PD-free survival over three months. Furthermore, we calculated the incremental cost-utility ratio (ICUR) across the experimental and control condition. The ICUR represents the incremental costs (or savings) per QALY (Quality Adjusted Life Years, assessed with the EQ-5D) gained in the experimental condition relative to the control condition. By calculating ICUR the results can be compared to other health care interventions. In all cases, uncertainty was assessed by means of non-parametric bootstrapping (2,500 times) of the data of the individual respondents.

All tests were conducted using a two-sided significance level at α < 0.05.

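### Incremental costs rest on raw pre-post differences; regression on baseline cost is never less precise in large samples and needs no new data

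*Protocol article*

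**What the plan says.** The economic part of the Analyses section (protocol article) sets out the cost calculation in two steps. First, "The mean total costs for each of the conditions at baseline and T1 were calculated". Next, "Then the pre-post difference in costs were calculated to obtain the increase (or decrease) of costs over time in each of the conditions". The text then goes straight to the ratios: "The incremental cost-effectiveness ratio (ICER) was calculated as the incremental costs for a health gain of a clinically significant change over three months". A second ICER, for being free of panic disorder, and an ICUR per QALY follow, both also built on incremental costs. On precision it says that "uncertainty was assessed by means of non-parametric bootstrapping (2,500 times) of the data of the individual respondents".

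No cost model that adjusts for baseline appears. The regression models earlier in the same section are for the clinical outcomes. Table 1 shows that the cost questionnaire (TIC-P) is completed at both T0 and T1. Under Study design, "A blocked randomization scheme was used, stratified by mental health centre, subthreshold PD versus mild PD", with agoraphobia as a further factor. Baseline cost is not a stratification factor.

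**The concern.** Subtracting baseline cost fixes the slope of T1 cost on T0 cost at 1. If the true slope is lower, subtraction over-corrects any chance imbalance in baseline costs and adds baseline noise to the comparison. Regression estimates the slope from the data. Randomisation makes both estimators unbiased, so the difference between them is one of precision.

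Incremental cost is the numerator of all three ratios, and cost-effectiveness is a stated aim of the trial. Extra noise there enlarges the cost component of the uncertainty. The bootstrap reports that noise but does not reduce it.

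**Working it through.** **Inputs from the article.** Sample size: "Power analysis indicated that 129 participants per condition are required", for a difference "equivalent to a standardized effect size of at least 0.35 in a two-sided test at alpha = 0.05" and "a power of (1-beta) = 0.80". Costs are measured at T0 and T1. The estimator is the pre-post difference per condition. No cost SD and no T0-T1 cost correlation is given, so rho and k below are assumptions.

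**The article's own figure.** n per arm = 2 × (1.960 + 0.842)² / 0.35² = 128.2, rounded up to 129. It reproduces; power at 129 per arm is 0.803. This figure concerns symptom reduction and serves here only as the planned arm size.

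**Variances.** Let SD0 and SD1 be the cost SDs at T0 and T1 (taken as the same in both arms), k = SD0/SD1, and rho the correlation. In units of 2·SD1²/n, the variance of the between-arm cost difference is:

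- T1 costs alone: 1
- change score: 1 + k² − 2·k·rho
- adjusted for T0 cost: 1 − rho²

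Change minus adjusted = k² − 2·k·rho + rho² = (k − rho)². This is never negative, and it is zero only when rho = k, that is, when the true slope rho/k equals 1. Change exceeds T1 alone when k² − 2·k·rho > 0, that is, when rho < k/2. That threshold is 0.5 for k = 1, 0.375 for k = 0.75 and 0.625 for k = 1.25.

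**Numbers.** The SE reduction from adjustment is 1 − √(adjusted/change). The last column is √change.

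| k | rho | change | adjusted | SE cut by adjustment | SE, change v T1 alone |
|---|---|---|---|---|---|
| 1 | 0.3 | 1.400 | 0.910 | 19% | 1.18 |
| 1 | 0.5 | 1.000 | 0.750 | 13% | 1.00 |
| 1 | 0.7 | 0.600 | 0.510 | 8% | 0.77 |
| 0.75 | 0.3 | 1.1125 | 0.910 | 10% | 1.05 |
| 0.75 | 0.5 | 0.8125 | 0.750 | 4% | 0.90 |
| 0.75 | 0.7 | 0.5125 | 0.510 | 0.2% | 0.72 |
| 1.25 | 0.3 | 1.8125 | 0.910 | 29% | 1.35 |
| 1.25 | 0.5 | 1.3125 | 0.750 | 24% | 1.15 |
| 1.25 | 0.7 | 0.8125 | 0.510 | 21% | 0.90 |

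Example for k = 1, rho = 0.3: √(0.910/1.400) = 0.806, a cut of 19%. With k = 1, a change-score analysis of 129 per arm is as precise as an adjusted one with 129 × (1 + rho)/2 per arm: about 84, 97 and 110 at rho = 0.3, 0.5 and 0.7.

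**Small-sample check.** Estimating the slope inflates the adjusted variance by about 1 + 1/(2 × 129 − 4) = 1.004. With k = 1, the change score could then win only for rho above 2/1.004 − 1, about 0.992.

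**Skewed costs.** A simulation used log-normal costs (log-SD 1.2, equal SDs, 129 per arm, 10,000 replicates). The ratio of change to adjusted SE was 1.28, 1.24 and 1.16 at raw correlations of about 0.24, 0.43 and 0.67. The formula gives 1.27, 1.18 and 1.09. The direction agrees, but the size depends on the assumed shape of the cost distribution.

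**The case against.** The strongest reply is that nothing here is wrong. The change score is unbiased, and bootstrapping individual data carries its variance into the reported uncertainty. A reader might infer that the ICERs are biased or their uncertainty misstated; the article does not support that. This reply stands, and it limits the point to efficiency.

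A second reply is that the size is unknown, and this also stands. A reader might infer that subtraction is worse than ignoring baseline whenever the correlation is below 0.5. That holds only if the two cost SDs are equal, and the article gives no SDs. If k = 0.5 and rho = 0.5, the gain from adjustment is exactly zero.

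Third, the ratios also carry uncertainty from their denominators (responders, PD-free participants, QALYs), which this choice does not touch. It would be too strong to say that every cost-effectiveness conclusion widens by the percentages above. The sample-size limit in Strengths and limitations concerns power for the incidence of panic disorder, not costs.

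Fourth, the article does not say in one sentence that the arms are compared on the differences. It is the natural reading, and no other cost estimator is offered, but it remains an inference from a condensed account.

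None of these replies gives a large-sample reason to prefer subtraction.

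**Conclusion.** The point holds as a recommendation on efficiency for a secondary economic outcome. On the natural reading of the Analyses section, the incremental cost is never more precise in large samples than a baseline-adjusted estimate. The direction does not depend on rho or k; the size does. Over assumed rho of 0.3 to 0.7 and k of 0.75 to 1.25, the SE cut runs from about 0.2% to 29%, and it is 8% to 19% if the SDs are equal. Only the cost component of the uncertainty narrows, and no effect on an ICER interval has been calculated.

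A reader might extend the argument to adjusting QALYs for baseline EQ-5D. The article does not say how QALYs are computed, so no fault is shown there.

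**What to change.** Within each of the 2,500 bootstrap replicates, estimate incremental cost from a linear regression of T1 total cost on arm and T0 total cost. Use the arm coefficient as the numerator of both ICERs and the ICUR. Where cell sizes allow, add the randomisation factors (centre, subthreshold versus mild PD, agoraphobia) as main effects. The number of centres is not given, so a full cross-classification could leave sparse cells in some replicates. Define incremental cost in one sentence so that the estimator need not be inferred. The simple pre-post difference can stay as a descriptive result.

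No new data are needed, since TIC-P is already collected at T0 and T1. The cost is a change of wording and code or, because the article reports these calculations in the past tense, possibly a re-run of the economic analysis.

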The sample can be divided in two groups: people with relatively mild manifestations of MINI-DSM-IV panic disorder and those with subthreshold manifestations not meeting the diagnostic criteria. When we focus on the latter group: people at risk of developing panic disorder, we can look at how many of these persons developed PD meeting the diagnostic criteria of the DSM-IV at T1. When we pay attention to the group with mild PD, we can see how many of these persons became PD-free at T1. For the primary outcome on the MINI-Plus we compared the proportion of success across the two groups. Success was defined as: (a) the participant had no PD at T0 and stayed PD free at T1 or (b) the participant had mild PD at T0 and no PD at T1. This yields a binary outcome where failure is coded 0, and success is coded 1. In a next step, this binary outcome was used to obtain the OR and the NNT.

The demographic and clinical characteristics of responders versus non-responders, and success versus failure, were compared using Student's *t *test for independent groups or Pearson's chi-squared tests when appropriate.

For the secondary outcomes on continuous measurement scales, a Gaussian regression model was used to test the hypothesis of superior intervention effects in the experimental arm compared to the wait-list control group. Furthermore, the between-group effect sizes (Cohen's *d*) were calculated. To test the maintenance of the effects at six-month follow-up we used a paired-samples t test to analyze the difference in mean score of the self-report measures in the experimental group from T0 to T1, T0 to T2 and T1 to T2.

To provide a more comprehensive picture of the effects of the intervention, results for the outcomes will also be presented for completers only (defined as participants who attended at least six sessions).

The following variables will be examined as potential mediators: cognitive aspects of panic disorder, symptoms of agoraphobia, anxiety and mastery. Furthermore, potential moderating variables (e.g., socio-demographic characteristics, panic disorder, agoraphobia, treatment credibility and mastery) will be analyzed.

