## Discussion

The purpose of this study is to evaluate the effectiveness of this early intervention based on cognitive behavioural principles on the reduction of panic disorder symptomatology. Furthermore, cost-effectiveness of the intervention is evaluated. We predicted that the experimental condition would show superior effects in reducing panic symptoms, improving quality of life and will be cost-effective despite the additional costs introduced by offering the 'Don't Panic' intervention in the first place. This may be regarded to be an important finding, because, to our knowledge, this is the first study that examines the effectiveness of an early intervention for self-referred adults with subthreshold or mild panic disorder, offered by community mental health centres.

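### The second ICER counts only participants who stayed PD free, whereas the MINI-Plus primary outcome also counts recovery from mild PD

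*Protocol article*

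**What the plan says.** All of the relevant text is in the protocol article, Methods, Analyses.

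- **MINI-Plus primary outcome.** Success has two routes, both judged at the posttest: "the participant had no PD at T0 and stayed PD free at T1 or (b) the participant had mild PD at T0 and no PD". Both routes count equally, and the result is one binary outcome over the whole sample.
- **Vocabulary.** Just before that definition, the text says of the mild PD group: "we can see how many of these persons became PD-free at T1". In the definition itself, *stayed* is used only for people without PD at T0.
- **Costs.** In the economic paragraph: "The mean total costs for each of the conditions at baseline and T1 were calculated". The pre-post difference is then taken per condition. No restriction to the subthreshold stratum is stated.
- **First ICER.** It uses the PDSS-SR responder outcome, unchanged from its definition as a primary outcome.
- **Second ICER.** The effect is introduced with "Next, we observed how many people stayed PD free at T1", and the ratio is the "incremental costs for a health gain of a PD-free survival over three months".

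**The concern.** A participant who has PD at T0 cannot stay PD free. Taken at its word, the second ICER therefore leaves out route (b) of the success definition, "the participant had mild PD at T0 and no PD at T1". The costs of those same participants remain in the condition means. A recovery from mild PD counts as success in the effectiveness analysis and as no benefit in the economic one.

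Two things follow. A reader who sets the second ICER beside the MINI-Plus odds ratio and NNT would assume that all three describe the same outcome, and they would not. The ratio would also rest on prevention of onset alone. The Strengths and limitations section concedes that adding mild PD left the trial short of power for incidence of PD on the MINI-Plus, so this is the part of the effect that the trial can estimate least well.

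**Working it through.** **Plan's own figures.** The article states no ICER, so there is no economic figure to reproduce. The one design figure that can be checked, 129 per condition for a standardised effect of 0.35 (two-sided 0.05, power 0.80), does reproduce, with a power of 0.803 at that size. The present point does not depend on it.

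**Notation**

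- s: share of each arm with subthreshold PD (no MINI-Plus PD at T0). Randomisation was stratified on subthreshold versus mild PD, so one s for both arms is reasonable.
- da: difference between arms in the proportion staying PD free, among subthreshold participants (prevention gain).
- db: difference between arms in the proportion with no PD at T1, among mild PD participants (remission gain).
- dC: incremental cost per participant, whole arm against whole arm.

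**Effect under each definition, over all randomised**

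- Literal (*stayed PD free*): dE = s·da
- MINI-Plus success: dE = s·da + (1−s)·db

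**Ratio of the two ICERs.** Both have the same dC, which cancels:

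[dC / (s·da)] ÷ [dC / (s·da + (1−s)·db)] = 1 + (1−s)·db / (s·da)

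**Inputs.** The document gives none of s, da or db for this trial. Those used here are assumptions:

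- s = 0.5.
- da = 0.059. The Background cites a six-month prevention trial in college students with PD onset of 13.6% against 1.8%, a difference of 11.8 points. Half of that, as a rough allowance for three months, is 5.9 points.
- db = 0.10 to 0.25.

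**Results**

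| db | dE literal | dE MINI-Plus success | Factor |
|---|---|---|---|
| 0 | 0.5 × 0.059 = 0.0295 | 0.0295 | 1.0 |
| 0.10 | 0.0295 | 0.0295 + 0.5 × 0.10 = 0.0795 | 0.0795 / 0.0295 = 2.7 |
| 0.25 | 0.0295 | 0.0295 + 0.5 × 0.25 = 0.1545 | 0.1545 / 0.0295 = 5.2 |

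**Sensitivity.** With s from 0.3 to 0.7 and db from 0.10 to 0.30, the factor runs from 1.36 to 6.93 at da = 0.118, and from 1.86 to 15.0 at da = 0.05. The width of these ranges shows how little can be said about size from the document. The factor is above 1 whenever da and db are both positive.

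**The case against.** The strongest reply is that *stayed PD free* is loose shorthand. The economic paragraph runs in parallel: first the PDSS-SR outcome, then the MINI-Plus outcome just defined. The sentence speaks of people in general and does not say that participants with PD at T0 are left out. Mild PD was added by a protocol change, so the wording may also be left over from a prevention-only design. Either is possible, and the document does not settle it. But the same section separates *stayed* from *became*, and the economic text uses only the former. If shorthand was meant, the correction is one of wording only.

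A second reply is that the literal measure is legitimate: cost per additional person remaining PD free, in a secondary analysis that need not share its unit with a primary outcome. It is computable, and this limits the point. A reader might infer that numerator and denominator must come from different populations. They need not, because the proportion who stayed PD free can be taken over each whole arm, as in the calculation above. What stands is that this narrower measure is not the trial's MINI-Plus outcome, and the text does not present it as something different.

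Three further inferences are tempting and are not supported.

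- *That the cost of delivering the course is left out.* The article ties the listed costs to the TIC-P and does not name the course. However, direct health-care costs head that list and may include it, and the Discussion expects cost-effectiveness "despite the additional costs introduced by offering the" course. Silence in a condensed article is not evidence of omission.
- *That the word survival signals a wrong method.* No time-to-event analysis is stated. The term can simply mean status at the end of a fixed interval, so this is terminology.
- *That the ratio necessarily overstates the cost of a gain.* That needs da and db both positive and positive incremental costs. With savings, the ratio is negative and the phrase does not apply.

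**Conclusion.** The point holds as an inconsistency between two definitions in the Analyses section. As written, the second ICER averages costs over each whole condition and credits only participants who were PD free at T0 and remained so. It therefore does not correspond to MINI-Plus success.

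The size is conditional. With a positive prevention gain and a positive remission gain, the absolute value of the ICER is inflated by 1 + (1−s)·db/(s·da). That is about 2.7 to 5.2 under the assumed s = 0.5, da = 0.059 and db = 0.10 to 0.25. With db = 0 the two ratios coincide. None of these inputs comes from the trial, so the figures show that the choice of definition can matter and do not estimate the error.

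The reach is limited to one of three secondary economic ratios. The PDSS-SR ICER, the ICUR and all the effectiveness analyses are unaffected.

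**What to change.** Define the effect in the second ICER as MINI-Plus success exactly as in the primary analysis, with both routes and over all randomised participants. Label it *cost per additional participant PD free at T1* in place of the survival wording.

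If a ratio for prevention alone is also wanted, take both costs and effects from participants without PD at T0, and present it as a separate subgroup result.

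The cost is a change of wording and, if the literal definition was programmed, a re-run of the planned 2,500 bootstrap samples. No new participant data are needed.

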### Interventions

We developed an early intervention for panic symptoms, called the 'Don't panic' course. The course is based on cognitive-behavioural principles and makes use of interventions that have appeared effective in the treatment of the full-blown disorder [27-29]. This intervention was developed specifically for adults. It consists of eight weekly sessions of two hours each in groups of six to 12 participants. The 'Don't panic' course makes use of a course manual [30], to be used by the psychologist and prevention worker offering the intervention, and an accompanying workbook for the participants [31]. The course instructors received a one-day training in offering the course and working with the course manual, to ensure integrity of the intervention delivery. Participants were taught to examine their panic attacks and the possible causes, to use techniques to influence their anxiety, and to develop skills to improve how they cope with panic attacks. The course includes (a) a psycho-educational element about the nature and physiology of anxiety and panic attacks, (b) life-style changes to improve physical condition, (c) stress management to prevent constant tension by learning effective ways to cope with stress, (d) relaxation training to reduce physiological arousal, (e) cognitive restructuring to challenge and correct dysfunctional cognitions of panic and anxiety, (f) interoceptive exposure to reduce the fear of somatic sensations, (g) 'in vivo' exposure to reduce agoraphobic avoidance, and (h) techniques aimed at relapse prevention. During the course the participants had to evaluate their progress. After three months following completion of the course a booster session was offered. Each session was structured to include a discussion of homework assignments, feedback, rehearsals, information about the upcoming topic and practical skills training. The intervention was extensively pilot-tested before entering the clinical trial stage.

The control condition consisted of a waiting list. Waitlisted people were told that they could start the course after four months. They were not kept waiting for the extended follow-up for ethical reasons.

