### Analyses

All analyses were conducted in agreement with the intention to treat principle [56], hence all participants were analyzed in the condition to which they were randomized, and missing endpoints at follow-up were imputed using a regression model with the best available predictors of outcome and the best predictors for dropout. The first set of predictors is required to get the most precise estimates for the missing values; the latter to correct for bias that may stem from differential loss-to-follow-up associated with T0 variables [57].

In all analyses on effectiveness, we controlled for the clustering of data caused by the multi-site character of the study. Clustering violates the assumption of independence of observations, and may thus affect standard errors and *P *values. So-called 'robust standard errors' and correct *P *values were obtained using the first-order Taylor series linearization method. All analyses were conducted with Stata 9.0 [58].

For the primary outcome on PDSS-SR, a Gaussian regression model was used to test the hypothesis of superior intervention effects in the experimental arm compared to the waitlist control group. We calculated between-group effect sizes at posttest by subtracting the mean posttest score of each condition and dividing the difference by the pooled standard deviation (Cohen's *d*). In the field of psychological interventions, effect sizes in the range of 0.00 to 0.32 are regarded as small, while effect sizes of 0.33 to 0.55 are moderate, and effect sizes of 0.56 to 1.2 are large [59].

As primary outcome we also compared the proportion of participants manifesting a clinically significant change on the PDSS-SR (responders) across the two groups. Clinically significant change was defined according to the criteria proposed by Jacobson and Truax [60]: a change should move from a dysfunctional distribution to a functional one, and the change should be statistically reliable in the sense that the observed change cannot be put down to measurement error in the PDSS-SR. Because we studied a population with subthreshold and mild PD, we considered scores below one standard deviation of the mean pretest score on the PDSS-SR as falling within the functional range [61]. This binary outcome was then used to obtain the odds ratio (OR) using a logistic regression of the binary outcome on the intervention dummy and the numbers-to-be-treated (NNT) using Gaussian regression.

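### The economic bootstrap resamples individuals although the course is given in groups in one arm only, so the uncertainty of the ICERs and ICUR may be understated if costs or effects correlate within course groups

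*Protocol article*

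**What the plan says.** All places are in the Methods of the protocol article.

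- **Analyses, economic evaluation.** Two ICERs (per clinically significant change on the PDSS-SR and per PD-free survival, both over three months) and an ICUR per QALY are calculated. For all of them, "uncertainty was assessed by means of non-parametric bootstrapping (2,500 times) of the data of the individual respondents". No course group, centre or stratum is named.
- **Interventions.** The course runs as "eight weekly sessions of two hours each in groups of six to 12 participants". For the other arm, "The control condition consisted of a waiting list". Before the three-month assessment there are therefore groups in one arm only.
- **Analyses, effectiveness.** "In all analyses on effectiveness, we controlled for the clustering of data caused by the multi-site character of the study". The reason given is that "Clustering violates the assumption of independence of observations, and may thus affect standard errors". The correction is by robust standard errors and concerns site. Course group is not mentioned.
- **Study design.** "A blocked randomization scheme was used, stratified by mental health centre, subthreshold PD versus mild PD, and by presence versus absence of co-occurring agoraphobia". Individuals are randomized within centre.

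**The concern.** A bootstrap of individuals treats them as independent. People in the same course group share instructors, fellow participants and eight sessions, so their outcomes, and perhaps their costs, may be correlated. The waitlist arm has no such source of correlation. The article names its resampling unit, so this is a stated rule that does not match the design, not a detail left to a fuller plan.

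The handling also differs within one section. The proportion with a clinically significant change on the PDSS-SR is a clinical outcome and also the effect measure of the first ICER. In the clinical analysis it gets site-robust standard errors. If course groups lie within centres, which delivery by community mental health centres suggests, those errors also absorb group correlation. In the economic analysis it gets neither.

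At stake is how certain the cost-effectiveness result appears. Point estimates are not affected.

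**Working it through.** **1. The plan's own figure.** The article states no standard error or interval for the economic results. Its one checkable figure is 129 per condition. With effect size 0.35, two-sided alpha 0.05 and power 0.80, 2 × ((1.960 + 0.842)/0.35)² = 128.14, which rounds up to 129. It is reproduced.

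**2. Inputs.** Group size m = 6 to 12, midpoint 9 (Interventions). Groups in one arm only (Interventions). Equal arms (Sample size). ICC within course group: not in the documents, assumed 0 to 0.10. No centre effect at this step.

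**3. Formulas, for one incremental difference in cost or effect.**

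- Design effect in the experimental arm: DE = 1 + (m − 1) × ICC; in the waitlist arm it is 1.
- Variance inflation of the difference: (DE + 1)/2.
- Individual-bootstrap SE / true SE: 1/√((DE + 1)/2).
- Actual coverage of a nominal 95% interval: 2Φ(1.96/√((DE + 1)/2)) − 1.

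Example, m = 9 and ICC = 0.05: DE = 1 + 8 × 0.05 = 1.40; inflation = 2.40/2 = 1.20; √1.20 = 1.095; 1/1.095 = 0.913, so the SE is understated by about 9%; coverage 92.6%.

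| ICC | m = 6: SE ratio, coverage | m = 9 | m = 12 |
|---|---|---|---|
| 0 | 1.000, 95.0% | 1.000, 95.0% | 1.000, 95.0% |
| 0.01 | 0.988, 94.7% | 0.981, 94.5% | 0.974, 94.4% |
| 0.02 | 0.976, 94.4% | 0.962, 94.1% | 0.949, 93.7% |
| 0.05 | 0.943, 93.5% | 0.913, 92.6% | 0.886, 91.7% |
| 0.10 | 0.894, 92.0% | 0.845, 90.2% | 0.803, 88.5% |

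**4. Adding a centre effect.** Randomization within centre removes a shared centre effect from the treatment contrast, but an unstratified individual bootstrap keeps that variance and so errs on the wide side. A simulation of 20,000 runs assumed 14 centres, one group of 9 each (14 × 9 = 126 per arm), and used the large-replicate limit of each bootstrap SE. The group bootstrap in the last column was not stratified by centre.

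| Group ICC | Centre ICC | Individual-bootstrap SE / true SE | Coverage, individual | Coverage, group |
|---|---|---|---|---|
| 0 | 0 | 0.988 | 94.9% | 93.9% |
| 0.05 | 0 | 0.910 | 92.6% | 93.8% |
| 0.10 | 0 | 0.833 | 89.4% | 93.4% |
| 0 | 0.05 | 1.022 | 95.4% | 96.2% |
| 0.02 | 0.05 | 0.969 | 94.1% | 95.8% |
| 0.05 | 0.05 | 0.931 | 93.1% | 95.7% |
| 0.05 | 0.10 | 0.943 | 93.6% | 97.1% |
| 0.01 | 0.10 | 1.029 | 95.6% | 97.7% |

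The centre effect shrinks the understatement, and with a very small group ICC the individual bootstrap becomes slightly too wide.

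**5. Number of groups.** 129/12 = 10.75 and 129/6 = 21.5, so roughly 11 to 22 course groups, about 14 at size 9.

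**The case against.** The strongest case against runs as follows, and much of it stands.

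- **The narrowing is conditional.** It needs a positive course-group ICC for costs, response or utility, and the documents give none. At ICC 0 nothing is lost; at 0.01 the loss is 1% to 3%. This stands. A reader might infer that the economic intervals are too narrow as a matter of fact; the documents do not support that.
- **The centre effect works the other way.** This stands, as step 4 shows. It weakens the effect and can change its sign, but it does not make the resampling rule fit the design.
- **The article's clustering statement concerns site, not course group.** This stands. A reader might infer that the article contradicts itself, or that the economic interval must be narrower than the clinical one. Neither follows: the correction is confined to effectiveness and to site, and site clustering with randomization within site tends to make an individual bootstrap conservative.
- **The PD outcomes are not identical.** Clinical success on the MINI-Plus includes remission of mild PD, whereas the economic section counts people who remained PD-free. This stands. Only the responder outcome is clearly shared.
- **The figures are for a single mean difference, not for a ratio.** This stands. They describe each component feeding the ICERs and ICUR. One ICC need not serve costs, response and QALYs alike, and 88.5% is the extreme corner of the range.
- **A group bootstrap with few groups is imperfect too.** This stands and shapes the fix.

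**Conclusion.** The point holds in conditional form. The stated resampling unit ignores group delivery in the experimental arm. If costs or effects correlate within course groups, the uncertainty of each incremental difference is understated, by 0% to about 20% of the SE over ICC 0 to 0.10 and groups of 6 to 12. The central illustration (size 9, ICC 0.05) is 9%, with coverage of about 92.6%. These figures rest on an assumed ICC, equal arms, a normal approximation and no centre effect; a shared centre effect reduces them and can reverse the direction at a very small group ICC.

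The consequence is small to moderate and falls on a secondary outcome. The change is still worth making, because cost-effectiveness is one of the article's stated predictions and the correction is cheap.

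**What to change.** Replace the individual bootstrap for the ICERs and the ICUR by one that:

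- resamples whole course groups in the experimental arm and individuals in the waitlist arm;
- keeps experimental-arm participants who never joined a group, as clusters of one, in line with intention to treat;
- keeps each person's cost and effect together in every replicate;
- accounts for centre where centres ran more than one group, but does not resample groups within a centre that ran only one, since that group would be drawn every time and its variation lost.

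The 2,500 replicates can stay. Report the observed course-group ICC for costs, response and utility, and show the individual-level bootstrap as a sensitivity analysis.

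The cost is a few lines of code and the course-group and centre identifiers; no new data collection. Intervals will be somewhat wider. With roughly 11 to 22 groups coverage is only approximate: in the simulation the group bootstrap that ignored centre covered 93.4% to 93.9% without a centre effect and 95.7% to 97.7% with one, which is why centre needs attention.
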